## General Information

This document describes the CASTLE trial including detailed information about procedures and recruitment. The protocol should not be used as an aide-memoir or guide for the treatment of other patients; every care was taken in its drafting, but corrections or amendments may be necessary. These will be circulated to the registered investigators in the trial, but centres entering patients for the first time are advised to contact the coordinating centre (CTRC) to confirm they have the most up to date version. Clinical problems relating to this trial should be referred to the Chief Investigator, [name], via the CTRC.

This protocol defines the participant characteristics required for trial entry and the schedule of treatment and follow-up. Participant recruitment will be undertaken in compliance with this document and applicable regulatory and governance requirements; waivers to authorise non-compliance are not permitted.

Incidence of protocol non-compliance, whether reported prospectively (e.g. where a treatment cannot be administered on a scheduled date as a result of public holidays) or retrospectively noted (e.g. as a result of central monitoring) are recorded as protocol deviations, the incidence of which is monitored and reported to trial oversight committees.

The template content structure is consistent with the SPIRIT (Standard Protocol Item: Recommendations for Interventional Trials 2013) and has regard for the Health Research Authority guidance. Regulatory and ethical compliance information is located in section 12.

## Relationship Statements

Roles and responsibilities are fully described in section 15.

The co-sponsors, King's College Hospital NHS Foundation Trust and King's College London, will formally delegate specific sponsoring roles to the King's Health Partners Clinical Trial Office (KHP CTO), Chief Investigator and Clinical Trials Unit, but remain legally responsible for the trial.

The KHP CTO Quality Team was established in 2008 to manage the Sponsor responsibilities for Clinical Trials of Medicinal Products (CTIMPs), as defined in the Regulations, for trials sponsored or co-sponsored by King's Health Partner Organisations. The KHP CTO also assists Chief Investigators with the set up and initiation of their trial and to ensure that these trials are conducted according to GCP and the Regulations, throughout the life of the trial.

Clinical Trials Unit: The CTRC at the University of Liverpool in collaboration with the Chief Investigator, [name], will have overall management responsibility for the trial and will be responsible for the co-ordination of centres.

CTRC, as part of the Liverpool Clinical Trials Collaborative, has achieved full registration by the UK Clinical Research Collaboration ([www.ukcrc.org](http://www.ukcrc.org)) as their standards and systems were assessed by an international review panel as reaching the highest quality. CTRC has a diverse trial portfolio underpinned by methodological rigour, a GCP compliant data management system, and core standard operating procedures.

## GLOSSARY

|          |                                                                  |
|----------|------------------------------------------------------------------|
| ABPI     | Association of the British Pharmaceutical Industry               |
| AE       | Adverse Event                                                    |
| AED      | Anti-Epileptic Drug                                              |
| AR       | Adverse Reaction                                                 |
| A&E      | Accident & Emergency                                             |
| BECTS    | Benign Epilepsy with Centrotemporal Spikes                       |
| CBZ      | Carbamazepine                                                    |
| CHEQOL   | Health Related Quality Of Life In Children With Epilepsy         |
| CI       | Chief Investigator                                               |
| CRF      | Case Report Form                                                 |
| CSHQ     | Children's Sleep Habits Questionnaire                            |
| CTRC     | Clinical Trials Research Centre                                  |
| EEG      | Electroencephalography                                           |
| GDPR     | General Data Protection Regulation                               |
| GP       | General Practitioner                                             |
| HEAP     | Health Economic Analysis Plan                                    |
| HES      | Hospital Episode Statistics                                      |
| HRA      | Health Research Authority                                        |
| HRQL     | Health Related Quality of Life                                   |
| HTA      | Health Technology Assessment                                     |
| ICO      | Information Commissioners Office                                 |
| IDSMC    | Independent Data and Safety Monitoring Committee                 |
| IEC      | Independent Ethical Committee                                    |
| ILAE     | International League Against Epilepsy                            |
| IPD      | Individual Participant Data                                      |
| ISF      | Investigator Site File                                           |
| ITT      | Intention To Treat                                               |
| KHP CTO  | King's Health Partners Clinical Trials Office                    |
| LEV      | Levetiracetam                                                    |
| MHRA     | Medicines and Health Care Products Regulatory Agency             |
| NICE     | National Institute for Health and Care Excellence                |
| NIHR CRN | National Institute for Health Research Clinical Research Network |
| NRES     | National Research Ethics Service                                 |
| NRLS     | National Reporting and Learning System                           |
| PBS      | Parent-Based Sleep Intervention                                  |
| PI       | Principal Investigator                                           |
| PIC      | Participant Identification Centre                                |
| PISC     | Patient Information Sheet and Consent                            |
| PLICS    | Patient-Level Information and Costing Systems                    |
| PPI      | Patient and Public Involvement                                   |
| PSAM     | Parenting Self-Agency Measure                                    |
| PSS      | Personal Social Services                                         |
| QA       | Quality Assurance                                                |

|       |                                                |
|-------|------------------------------------------------|
| QALYs | Quality-Adjusted Life-Years                    |
| QC    | Quality Control                                |
| QOL   | Quality of Life                                |
| RE    | Rolandic Epilepsy                              |
| R&D   | Research & Development                         |
| RCT   | Randomised Controlled Trial                    |
| REC   | Research Ethics Committee                      |
| RSI   | Reference Safety Information                   |
| SAE   | Serious Adverse Event                          |
| SAP   | Statistical Analysis Plan                      |
| SAR   | Serious Adverse Reaction                       |
| SDQ   | Strengths and Difficulties Questionnaire       |
| SDV   | Source Data Verification                       |
| SmPC  | Summary of Product Characteristics             |
| SOP   | Standard Operating Procedure                   |
| SUSAR | Suspected Unexpected Serious Adverse Reactions |
| TMG   | Trial Management Group                         |
| TSC   | Trial Steering Committee                       |
| UAR   | Unexpected Adverse Reaction                    |
| USM   | Urgent Safety Measure                          |

## 2 PROTOCOL SUMMARY

|                                        |                                                                                                                                                                                                                                                                                                                                                                                                                                                                                                                                                                                                                          |
|----------------------------------------|--------------------------------------------------------------------------------------------------------------------------------------------------------------------------------------------------------------------------------------------------------------------------------------------------------------------------------------------------------------------------------------------------------------------------------------------------------------------------------------------------------------------------------------------------------------------------------------------------------------------------|
| Full Title:                     | Randomised factorial design controlled trial comparing carbamazepine, levetiracetam or active monitoring combined with or without sleep behaviour intervention in treatment naive children with rolandic epilepsy                                                                                                                                                                                                                                                                                                                                                                                                        |
| Acronym:                        | CASTLE                                                                                                                                                                                                                                                                                                                                                                                                                                                                                                                                                                                                                   |
| Phase:                          | IV                                                                                                                                                                                                                                                                                                                                                                                                                                                                                                                                                                                                                       |
| Target Condition:               | Treatment naive children with rolandic epilepsy (RE) in the UK.                                                                                                                                                                                                                                                                                                                                                                                                                                                                                                                                                          |
| Sample size:                    | 330                                                                                                                                                                                                                                                                                                                                                                                                                                                                                                                                                                                                                      |
| Main Inclusion Criteria :       | 
 
a. Children diagnosed with RE
 
b. EEG showing focal sharp waves with normal background
 
c. Aged <math>\geq 5</math> years and <math>< 13</math> years at time of randomisation
 
d. Currently untreated with antiepileptic drugs
 
e. Written informed consent received from person with parental responsibility/legal representative
 
f. Family have a valid email address and regular internet access (for online sleep intervention)
 
g. Parent and child are to have a good understanding of the English language
 
 |
| Main Exclusion Criteria :       | 
 
a. Known contraindication to any trial drugs
 
b. Previously treated for epilepsy with antiepileptic drugs
 
                                                                                                                                                                                                                                                                                                                                                                                                                                                      |
| Trial Centres and Distribution: | UK secondary or tertiary centres for paediatrics.                                                                                                                                                                                                                                                                                                                                                                                                                                                                                                                                                                        |
| Participant Trial Duration:     | Minimum/Maximum 12/48 months                                                                                                                                                                                                                                                                                                                                                                                                                                                                                                                                                                                             |
| Overall Trial duration:         | 60 months                                                                                                                                                                                                                                                                                                                                                                                                                                                                                                                                                                                                                |
| Agent/ Interventions:           | 
Interventions:
 
 
(1) Oral carbamazepine or levetiracetam prescribed in a formulation and at a dose deemed suitable by the treating physicians and guided by ranges in summary of product characteristics (SmPC).
 
(2) Sleep behaviour intervention
 
 
Controls:
 
 
(1) No antiepileptic drug treatment (AED) – active monitoring
 
(2) No sleep behaviour intervention – standard care
 
                                                                                            |

|                             | Objectives                                                                                                                       | Outcome Measures                                                                                                                                                                    |
|-----------------------------|----------------------------------------------------------------------------------------------------------------------------------|-------------------------------------------------------------------------------------------------------------------------------------------------------------------------------------|
| Primary:             | To determine if carbamazepine or levetiracetam are superior to no AED with respect to time to 6- month seizure remission.        | Time to 6-month seizure remission based on seizure report                                                                                                                           |
|                             | To determine if a PBS intervention is superior to standard care with respect to 3-month sleep problem frequency measured by CSHQ | Total sleep problem score as measured by the CSHQ                                                                                                                                   |
| Primary (economic)*: | To estimate the cost-utility of carbamazepine, levetiracetam and PBS                                                             | Total costs based on resource use questionnaires, and routine hospital data; and quality-adjusted life years (QALYs) based on health utilities                                      |
| Secondary:           | To compare time to treatment failure due to inadequate seizure control or unacceptable adverse reactions                         | Time taken from randomisation to decision by child, parent or treating physician to be withdrawn from treatment due to inadequate seizure control or unacceptable adverse reactions |
|                             | To compare time to treatment failure due to inadequate seizure control                                                           | Time taken from randomisation to decision by child, parent or treating physician to be withdrawn from treatment due to inadequate seizure control                                   |
|                             | To compare time to treatment failure due to unacceptable adverse reactions                                                       | Time taken from recruitment to decision by child, parent or treating physician to be withdrawn from trial due to unacceptable adverse reactions                                     |
|                             | To compare time to first seizure                                                                                                 | Time to first seizure based on seizure report                                                                                                                                       |
|                             | To compare time to 12-month remission from seizures                                                                              | Time to 12-month seizure remission based on seizure report                                                                                                                          |

---

\* This has no implications for sample size calculation

|               |                                                                                                           |                                                                                                                                       |
|---------------|-----------------------------------------------------------------------------------------------------------|---------------------------------------------------------------------------------------------------------------------------------------|
|               | To determine if a PBS intervention is superior to standard care                                           | Total sleep problem score as measured by the CSHQ                                                                                     |
|               | To compare measures of cognition across the different treatment groups                                    | Total score in three chosen assessments delivered by CANTAB iPad Neuropsychological battery                                           |
|               | To compare Health Related Quality of Life across the different treatment groups                           | CHEQOL score change (1)                                                                                                               |
|               | To compare measures of children's behaviour across the different treatment groups                         | Total score on strengths and difficulties questionnaire (SDQ)                                                                         |
|               | To identify any adverse reactions and their rate                                                          | Records of adverse reactions                                                                                                          |
|               | To estimate child health utilities and QALYs across the different treatment groups                        | Score changes in:
1. CHU9D (2)
2. EQ-5D-Y                                                                                       |
|               | To estimate health utilities and QALYs across parents in the different treatment groups                   | EQ-5D-5L score change                                                                                                                 |
|               | To compare parenting self-efficacy across the different treatment groups                                  | Score changes in:
1. PSAM (3)                                                                                                      |
|               | To compare sickness related school absences across the different treatment groups                         | Total sickness related school absences (days)                                                                                         |
|               | To determine the costs to the NHS and personal social services (PSS)                                      | 1. Resource use questionnaire
2. Patient Level Information and Costing System (PLICS) data
3. Hospital Episode Statistics (HES) |
| Other: | To determine which sleep parameters change in primary carer and child dyads in different treatment groups | Summary of actigraphy variables (total sleep time/sleep latency/sleep efficiency) averaged over a 1 week period                       |

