| To compare time to 12-month remission from seizures                                                      | Time to 12-month seizure remission based on seizure report                                                                                                                          | 3,6,12 months and annually thereafter 'when was last seizure' question in clinic |
| To determine if a PBS intervention is superior to standard care                                          | Total sleep problem score as measured by the CSHQ                                                                                                                                   | At 12 months and annually thereafter                                             |
| To compare measures of cognition across the different treatment groups                                   | Total score in three chosen assessments delivered by CANTAB iPad Neuropsychological battery                                                                                         | At baseline, 3 and 12 months and annually thereafter                             |
| To compare Health Related Quality of Life across the different treatment groups                          | CHEQOL score change (1)                                                                                                                                                             | At baseline and 12 months and annually thereafter                                |
| To compare measures of children's behaviour across the different treatment groups                        | Total score on strengths and difficulties questionnaire (SDQ)                                                                                                                       | At baseline and 12 months and annually thereafter                                |
| To identify any adverse reactions and their rate                                                         | Records of adverse reactions                                                                                                                                                        | Adverse reactions at 3,6,12,24 months and annually thereafter in clinic          |

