**8.1.2 Schedule for Follow-up**

The expected duration of follow-up for each participant is between a minimum of 12 months and a maximum of 48 months, depending on the time of recruitment. All participants will be followed up whether they are still taking their allocated treatment or not. Where participants default from hospital follow-up, additional information will be sought at the end of the trial from GPs who will be the main prescribers of AEDs in this trial, and where necessary participants will be contacted directly for follow up information.

Participants will be followed up as per routine clinical practice and typically at 3, 6, and 12 months and annually thereafter, where applicable. Participants will be seen at other times as clinically indicated.

A visit window for the 3 month visit of +/- 2 weeks is allowed. Visit windows are not prescribed for the 6, 12 months or annual visits after that. A delegated member of the research team should complete the 'follow-up CRF' for the 3, 6, 12 month and annual visits. The visit which occurs at the nearest timepoint will be taken to be the record of the 3, 6, 12 months or other annual visits from randomisation.

In the event of an early trial termination, the schedule for follow up activities (including actigraphy and qualitative interviews) will be shortened accordingly to 6 months post-randomisation. This will occur following agreement by the TMG, IDSMC and Sponsor.

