##### **9.2.6.1 Data on Concomitant Medications**

Details of AED treatment and concomitant medications related to the treatment of adverse reactions are to be collected from trial entry until trial completion .

The PI or delegated research team member should reassess AED treatment and concomitant medications related to the treatment of adverse reactions at each trial visit and record any changes on the applicable CRF.

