A similar strategy will be used for the analysis of secondary time to event outcomes. For time to treatment failure, further analysis will be undertaken to assess the two main reasons for treatment failure - inadequate seizure control and unacceptable adverse effects. To allow for possible dependence between the different withdrawal risks, cumulative incidence analyses will be presented (34).

The Haybittle-Peto approach will be employed for each interim analysis, with 99.9% confidence intervals calculated for interim analysis effect estimates. The final analysis will be undertaken at the end of the trial when all participants have a minimum 12 months follow-up data and 95% confidence intervals will be calculated.

QOL data will be analysed longitudinally to explore between treatments changes in scale scores over time, taking account of baseline QOL.

Qualitative interview data will be analysed using an interpretive, reflexive and conceptual analytical approach. Data will be thematically analysed in discrete sets (e.g., the trial group and the non-trial groups, different treatments/management, different responses/experiences), and parents/primary carers' and children's transcripts will be analysed separately before considering each dyad and prior to synthesis of all the data.

For the analysis of safety events, all participants who received any amount of each trial drug will be included in the safety analysis dataset in the treatment group they actually received. All safety events reported by the clinical investigators will be presented, identified by treatment group. Safety events will be grouped according to a pre-specified coding system and tabulated. The number (and percentage) of participants experiencing each safety event, and the number (and percentage) of occurrences of each safety event will be presented. No formal statistical testing will be undertaken.

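### The adverse-reaction objective asks for a rate, but the planned percentages have no time base and are not comparable between drugs when time on drug differs

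*Protocol*

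**What the plan says.** The protocol summary (section 2) and Table 1 (section 3.3) list as a secondary objective "To identify any adverse reactions and their rate". The outcome is the record of adverse reactions, with the timing "Adverse reactions at 3,6,12,24 months and annually thereafter in clinic". No denominator or unit of time is given for the rate.

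Section 11.5.1 fixes the safety analysis. On the population, "all participants who received any amount of each trial drug will be included in the safety analysis dataset", in the group of the treatment actually received. On the summary, "The number (and percentage) of participants experiencing each safety event, and the number (and percentage) of occurrences of each safety event will be presented". It adds: "No formal statistical testing will be undertaken". The protocol does not say what the percentage of occurrences is a percentage of.

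Follow-up per child is "between a minimum of 12 months and a maximum of 48 months, depending on the time of recruitment" (section 8.1.2). Section 9.2.3 allows allocated drug to be discontinued at any time in the trial, and section 11.4 plans to monitor how many children move from no AED to an AED. Section 9.2.6.1 provides that "Details of AED treatment and concomitant medications related to the treatment of adverse reactions are to be collected from trial entry until trial completion".

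**The concern.** A child who took one dose and a child treated for four years each add one to the denominator. The planned percentage is therefore neither a rate per unit of time nor a risk over a stated period. It mixes how often reactions occur with how long children stayed on drug.

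Time on drug is not randomised. It may well differ between carbamazepine and levetiracetam: time to treatment failure is itself a secondary outcome. Because the safety groups follow treatment received, a child who moves from active monitoring to a drug enters that group late, with short exposure, and still counts as one full unit.

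At stake is the reading of a named secondary objective. Tables set out by treatment group will be used to judge which drug is better tolerated, whether or not a test is attached. The primary outcomes are not affected.

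**Working it through.** **The plan's own figure.** Section 2 (Figure 1 note) gives 36 months of recruitment and 12 months of follow-up after it closes. Maximum follow-up is 36 + 12 = 48 months and minimum 12, which agrees with "Minimum/Maximum 12/48 months".

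**Inputs that the protocol does not give.** It states no adverse-reaction hazard and no stopping rate. Every hazard below is an assumption chosen to show the mechanism.

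**One child.** With a constant hazard of 0.2 per year on drug, the chance of at least one reaction is 1 − exp(−0.2t): 0.05% after one day, 18% after 1 year, 55% after 4 years. Each such child has the same weight in the planned percentage.

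**Two drugs with the same hazard.** Let h be the hazard of a first reaction on drug, s the hazard of stopping for reasons unrelated to reactions, and F the follow-up, uniform on 1 to 4 years. Then

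- P(reaction on drug) = h/(h+s) × [1 − E(e^(−(h+s)F))], with E(e^(−kF)) = (e^(−k) − e^(−4k))/(3k)
- mean time on drug = [1 − E(e^(−sF))]/s

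For h = 0.25:

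- s = 0.2: k = 0.45, E = (0.638 − 0.165)/1.35 = 0.350, P = 0.556 × 0.650 = 36.1%. Mean time on drug 1.92 years.
- s = 0.6: k = 0.85, E = (0.427 − 0.033)/2.55 = 0.155, P = 0.294 × 0.845 = 24.9%. Mean time on drug 1.24 years.

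The true hazard is 0.25 per drug-year on both, yet the percentages differ by about 11 points. The same two stopping rates with other hazards:

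| h per year | s = 0.2 | s = 0.6 | Gap (points) |
|---|---|---|---|
| 0.15 | 24.2% | 16.2% | 8 |
| 0.25 | 36.1% | 24.9% | 11 |
| 0.40 | 49.7% | 35.3% | 14 |

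**Reactions clustered early.** Keep s = 0.2 and 0.6, but take a hazard of 1 to 2 per year for the first three months and 0.02 to 0.10 per year afterwards. The gap shrinks to between 2.0 points (24.2% vs 22.2%) and 5.5 points (33.3% vs 27.8%).

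**Stopping caused by reactions.** Take h = 0.4 with 80% of first reactions ending treatment, against h = 0.2 with none doing so, and other stopping at 0.1 per year on both. Mean time on drug is 1.53 vs 2.18 years, and the percentage with a reaction is about 55% vs 34%. Here the drug stopped sooner shows the higher figure, because a reaction that ends treatment is counted before exposure ends.

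**The case against.** The strongest reply has five parts.

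- **Direction.** A reader might infer that the drug stopped sooner will look safer. The documents do not support that as a general statement. Unacceptable reactions are one of the protocol's own reasons for stopping, and those reactions stay in the numerator. This part stands in full.
- **Follow-up range.** A reader might also infer that the 12 to 48 month spread biases the comparison. It depends on the date of entry, and concurrent 1:1:1 randomisation balances it in expectation. This stands for the randomised arms. It does not rescue the safety tables, which group by treatment received and ignore time on drug.
- **Meaning of rate.** The protocol uses the word loosely: section 11.4 speaks of follow-up and treatment failure rates, section 3.2.1 of an adverse reaction rate. On that reading a percentage is a rate, and objective and analysis do not contradict each other. This stands, but such a proportion still lacks a period to which it refers.
- **Covered elsewhere.** Time to treatment failure from unacceptable reactions is a secondary outcome, with cumulative incidence by reason. That handles reactions that end treatment and leaves tolerated reactions without any time-based summary.
- **Descriptive tables and the SAP.** No testing is planned, and an SAP not seen here could add exposure-adjusted figures. That limits the weight of the point. However, the protocol states this summary itself, so the place to improve it is section 11.5.1.

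**Conclusion.** The point holds in a limited form. The objective's rate has no time base, and the planned percentages ignore time on drug, so they do not compare carbamazepine with levetiracetam fairly when time on drug differs. The size cannot be taken from the protocol. Under the assumed values the gap at equal true hazards is 8 to 14 points with a constant hazard and stopping unrelated to reactions, and about 2 to 5.5 points if reactions cluster early. If reactions themselves cause the stopping, the ordering can go the other way. It would go too far to say that the trial reports no rate in any sense, or that the harm comparison favours the less acceptable drug. This is a cheap improvement to a secondary, descriptive analysis.

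**What to change.** In section 11.5.1, for adverse reactions on each drug:

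1. Add the number of reactions per 100 child-years on that drug, with a 95% confidence interval. Take time on drug from the AED treatment data, assuming these include start and stop dates.
2. Preferably add the cumulative incidence of a first adverse reaction by 12 months from starting the drug, with stopping the drug as a competing event. This gives a defined period and is the more informative figure if reactions cluster early, when a single rate per child-year averages unlike periods. It still reflects how often the drug is stopped, so the two should be read together.
3. Keep the number and percentage of children with each event as description.
4. State the denominator of the percentage of occurrences, or drop that column.

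The cost is a sentence or two in the protocol and the SAP, a few table columns and slightly more programming. No new data collection is needed if the dates are recorded as assumed.
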